## Abstract

**Background:**

The focus of Specialized Palliative Care (SPC) is to improve care for patients with incurable diseases and their families, which includes the opportunity to make their own choice of place of care and ultimately place of death.

The Danish Palliative Care Trial (DOMUS) aims to investigate whether an accelerated transition process from oncological treatment to continuing SPC at home for patients with incurable cancer results in more patients reaching their preferred place of care and death. The SPC in this trial is enriched with a manualized psychological intervention.

**Methods/Design:**

DOMUS is a controlled randomized clinical trial with a balanced parallel-group randomization (1:1). The planned sample size is 340 in- and outpatients treated at the Department of Oncology at Copenhagen University Hospital. Patients are randomly assigned either to: a) standard care plus SPC enriched with a standardized psychological intervention for patients and caregivers at home or b) standard care alone. Inclusion criteria are incurable cancer with no or limited antineoplastic treatment options.

**Discussion:**

Programs that facilitate transition from hospital treatment to SPC at home for patients with incurable cancer can be a powerful tool to improve patients’ quality of life and support family/caregivers during the disease trajectory. The present study offers a model for achieving optimal delivery of palliative care in the patient’s preferred place of care and attempt to clarify challenges.

**Trial registration:**

Clinicaltrials.gov Identifier: NCT01885637

## Background

The Capital Region of Denmark had in 2013 1,735,521 inhabitants with one of the highest incidences (0.6%) and prevalence (4.3%) of cancer in the world as well as a high cancer mortality rate (6.8%). Almost five thousand of the inhabitants of the Capital Region dies of cancer every year (0.25%) [1]. Thus, a substantial need for palliative cancer care is observed.

Studies have shown that most patients with advanced cancer prefer to spend the last part of their life at home (50-90%) [2,3]. However, in most western countries more than half of the patients with advanced cancer die in hospitals [3-9]. A recent systematic review by Gomes *et al.* showed that most people with different terminal diseases preferred to die at home and the majority of patients did not change preferences as their illnesses progressed [10]. Similar preferences were reported in a retrospective Danish survey, which indicated that the majority of cancer patients in the palliative care phase preferred to die in their own home (81%); however, the reported preference for dying at home decreased towards time of death (64%) [11]. Further, a recent prospective Danish study indicated that the majority (71%) of cancer patients in palliative care preferred to die in their own home [12]. According to the National Board of Health, 55% of Danish cancer patients died in hospitals, 18% in nursing homes or in specialist palliative care institutions, while only 26% died at home in 2005 [13]. A similar pattern is seen in other European countries, as the place of death in Europe is most frequently hospital or nursing home [14]. Even in the UK, which has a well-developed and comprehensive national palliative care system, a study analyzing all cancer deaths between 1993 and 2010 showed that 48% died in a hospital and 16% in hospices, while 25% died at home [15]. Timely and continuous involvement of General Practitioners (GP), nurses and - when necessary - a Specialized Palliative Care Team (SPT) seems to have a positive impact on the likelihood of dying at home [16,17]. Experience from the UK also showed that pronounced delay in the discharge from the hospital was a major obstacle to achieving the preferred place of palliative care and death [18].

In cancer care the availability of SPC seems to be a strong predictor for achieving home deaths [19-22]. A prospective study demonstrated that agreement and understanding between patients and informal caregivers about patients’ preferred place of palliative care seems to be a crucial prerequisite for obtaining death at home [23]. Grande and Ewing found that this consensus resulted in a substantial likelihood that the patient died at his or her preferred place [23]. It is interesting to note that place of death can be a proxy for place of care. A systematic review from 2006 explored the factors influencing death at home [24]. Among the main factors strongly associated with death at home, patient’s preference for home death and home care were clearly expressed [24].

Integration and coordination between oncological treatment, SPC and standard care may be the best way to organize the palliative care for patients with cancer [25]. This approach could give patients the advantage of timely access to care at home and simultaneous improvement of symptom control and quality of life [25]. Brumley *et al*. conducted a randomized controlled trial of palliative care at home with terminally ill patients (late-stage patients with cancer, chronic obstructive pulmonary disease, and congestive heart failure), which reported a significant increase in satisfaction with care 30 and 90 days after enrollment [26]. More patients died at home (71%) compared to those receiving standard care (51%) and the intervention group was less likely to visit emergency rooms or be admitted to hospitals (36% compared to 59% in the control group), resulting in significantly lower costs [26].

Another advantage of SPC at home is the possibility to support bereaved relatives and caregivers [27]. In most cases, the grief process is uncomplicated, however, for up to 15% of bereaved relatives grief may develop into a psycho-pathological condition [28]. The World Health Organization’s (WHO) definition of palliative care emphasizes that the informal caregivers’ health and needs should also be assessed and supported in palliative care [29]. Informal caregivers of patients with advanced cancer can experience deterioration of their own health and mental well-being [30]. Furthermore, caregivers’ wishes regarding the place of death for their loved ones and their perception of the social support they received seem to be significantly associated with place of death [31].

We also considered measures of telomere length in caregivers of cancer patients as a measure for an effect of the intervention. The pathophysiological consequences of caregiving have not been fully elucidated and several studies indicate that caregivers’ stress and strain may be associated with shorter telomere length, a marker of cellular aging. A study of 338 caregivers in the 2008–2010 Survey of the Health of Wisconsin observed significantly shorter telomere length associated with number of hours per week of caregiving, caring for a younger individual, and more strain. Caregivers with discordant levels of stress and strain (i.e., low perceived stress/high strain) compared with low stress/low strain had significantly shorter telomeres corresponding to approximately 10–15 additional years of aging [32].

Thus, the DOMUS study protocol will describe an investigation of accelerated transition from oncological treatment to SPC at home for patients with incurable cancer in order to support patients and their informal caregivers to reach and stay in their preferred place of care and death.

### Study objectives

The primary aim of DOMUS is to investigate whether an accelerated transition process from oncological treatment to SPC at home for patients with incurable cancer results in prolonged residence in their preferred place of care, which indirectly may increase the number of home deaths. The secondary aims are to investigate whether the intervention:

– relieves patients’ symptoms (pain, tiredness, drowsiness, nausea, vomiting, dyspnea, insomnia, appetite, constipation, and diarrhea)

– improves patients’ and the closest relatives’ quality of life (health related quality of life)

– relieves patients’ as well as caregivers’ psychosocial problems (depression, anxiety, dyadic coping, and caregiver burden)

– ameliorates the bereavement process among the closest relatives (anxiety, depression, loss- and restoration-oriented coping, prolonged grief, sleep, lifestyle)

– prolongs survival of patients

improves cooperation between professionals

– is cost-effective

## Methods/Design

### Study design

DOMUS is a controlled randomized clinical trial (RCT) with a balanced parallel-group randomization (1:1). Three-hundred-and-forty in- and outpatients in the Department of Oncology, Copenhagen University Hospital, will be randomly assigned to either an accelerated transition from oncological treatment to standard care plus continuing SPC enriched with a manualized psychological intervention at home (including nursing home) or standard care alone (Figure 1). The transition does not mean that oncological treatment has to be finalized.

**Figure 1 F1:**
[figure not shown]
Description of the content of the intervention and the control group.

### Patient selection

Inclusion and exclusion criteria are demonstrated in List of Inclusion and exclusion criteria of the DOMUS study:

### List of Inclusion and exclusion criteria of the DOMUS study

#### **
*Inclusion criteria*
**

– Adult (at least 18 year old) cancer patients treated at the Department of Oncology, Copenhagen University Hospital

– Patients who want to spend as much time as possible in their own homes supported by a SPT

– Patients with incurable cancer

– Patients with no or limited antineoplastic treatment options^a^ or patients who resign antineoplastic treatment

– Patients living in the Capital Region, Denmark

– Written informed consent

a) Limited antineoplastic treatment options are specified in Table 1.

SPT = specialized palliative care team.

#### **
*Exclusion criteria*
**

– Patients who have already been referred to a SPT

– Hospitalized patients who are not judged capable of being discharged home

– Patients who are admitted to other hospitals

– Patients who do not speak Danish well enough to answer the questionnaires

– Patients who are considered incapable of cooperating in the trial

#### **
*Inclusion criteria for caregivers*
**

– Adults (at least 18 years of age)

– Written informed consent (in addition to that from the patient)

All included patients live in the Capital Region and are treated at the Department of Oncology, Copenhagen University Hospital. Limited antineoplastic treatment options listed in the inclusion criteria are dispelled in Table 1. A standard procedure is implemented to ensure that patients with varied diagnosis from the different clinics are screened evenly. In practice, it means that inpatients are screened on a daily basis and outpatients are screened following a sequential alternation procedure that guarantees an equal screening frequency of the six outpatient clinics involved in this study.

**Table 1 T1:** Definition of limited antineoplastic treatment options

**Disease**	**Limited treatment options**
Breast cancer	Refractory to 3rd line antineoplastic treatment for metastatic disease
Lung cancer	Refractory to 1st line chemotherapy for metastatic/advanced disease
Gastrointestinal cancers	Refractory to 1st line chemotherapy for metastatic/advanced disease
Ovarian cancer/Uterine cancer	Refractory to 2nd line chemotherapy for metastatic/advanced disease
Cervical cancer/Vulva cancer	Refractory to 1st line chemotherapy for metastatic/advanced disease
CNS tumors	Refractory to concomitant/adjuvant chemotherapy
Prostate cancer/Bladder cancer/Penile cancer/Thyme cancer/Adrenal carcinomas	Refractory to 1st line chemotherapy for metastatic/advanced disease
Cancer of Unknown Primary origin (CUP)	Refractory to 1st line chemotherapy for metastatic/advanced disease
Head and neck cancer	Refractory to radiation therapy or surgery with curative intention

### Recruitment

Project nurses recruit patients from the oncology wards and outpatient clinics. From June 2013 to June 2015 three project nurses daily screen in- and outpatients from the Department of Oncology, Copenhagen University Hospital, and contact selected patients after having examined medical records to determine whether the patients are eligible for inclusion in the trial.

Before the patient agrees to participate in DOMUS, an information meeting will be held, to give the patients and closest relative oral and written information about the trial. If the patient gives consent to participate, an informal caregiver, appointed by the patient, is also invited to participate. Upon consent, the baseline questionnaires will be completed followed by randomization of the patient. A blood sample will be taken from the caregiver within a week to measure the leukocyte telomere length (a stress level marker).

### Randomization

The randomization is computer-generated by a statistician who is not attached to the project, the allocation sequence and block size are unknown to the involved nurses, who recruit patients and collect data. The allocation ratio will be 1:1. After the patient have given informed consent and filled out the baseline questionnaire, the nurses draw a sealed envelope, which is packed by uninvolved staff and contains information about randomization group.

### Intervention group

In the intervention group several steps will take place. A meeting is held with a research nurse one or two days after randomization, where the patient (and informal caregiver) discusses the patient’s wishes for treatment and care at home and how these can be reconciled with the caregiver’s wishes. The patient and caregiver’s perceptions of challenges and concerns related to home care are explored and addressed. Shortly after the meeting, any necessary changes regarding the home interior are planned.Four to five days after randomization a home conference is held including the patient, caregiver, representatives of the SPT, a district nurse, and if possible the GP and project psychologist. The SPT, in collaboration with the GP and the district nurse, is now responsible for the distribution of tasks related to further treatment and care (Figure 1).

Only two of nine SPTs in the Capital Region have psychologists to support and treat patients and their relatives in their homes [33]. Therefore, in order to support patients and caregivers included in the intervention group, a standardized psychological intervention along with the regular SPT intervention (physician and nurse) is added. Patients and caregivers receive a psychological supportive care intervention, beginning after the home conference. The intervention is conducted based on a manual, developed for the DOMUS trial to describe and standardize the use of a joint patient-caregiver psychological intervention in a palliative care setting.

### Control group

In the control group, the patients follow current practice in the healthcare system, being standard care as described below. If the patient is allocated to the control group, an additional meeting with the patient and the informal caregiver will be offered to clarify the options available in case of unmet palliative needs. A patient allocated to the control group can obtain equivalent elements of treatment and care as a patient allocated to the intervention group; however, the flow and sequence may be different.

### Standard care

Patients allocated to both groups will remain patients of the Department of Oncology at Rigshospitalet and continue oncological treatment if the oncologist find it relevant. General care provided according to the precepts of the Danish healthcare system includes in-hospital treatment as well as a GP, a GP out-of-hours service and access to 24-hour home nursing or nursing homes. Patients and caregivers may – if needed - receive psychological counseling through referral from their GP. Patients can be referred to SPC if their GP and/or oncologist judge this to be relevant. The current practice is referral due to complex palliative care needs.

The Danish healthcare system is financed through taxes and is free of charge at the point of receipt.

### Specialized palliative care

The definition of SPC in Denmark is based on the European Associations of Palliative Care’ statement [14]: “Specialist palliative care services require a team approach, combining a multi-professional team with an interdisciplinary mode of work. Team members must be highly qualified and should have their main focus of work in palliative care” [14]. At the moment 18 hospices, four hospital wards and 28 SPTs fulfill these requirements throughout the country. In the Capital Region there are nine SPTs; four of them are hospice-based and five are hospital-based [33].

### Assessments

Project nurses collect baseline data from patient records regarding the medical history of the included patients. Patients and caregivers are asked to complete questionnaires (Table 2) before they are randomized and after 2, 4, and 8 weeks and 6 months. Caregivers (bereaved) will be asked to fill in questionnaires (Table 2) two weeks and 2, 7, 13 and 19 months after the patient’s death. The selection of questionnaires was based on previous experience, validation and availability in the Danish language. As we do not want to burden the participants it is stated in each of the questionnaires that patient/caregiver/bereaved are welcome to fill it in over two days. Each questionnaire package is estimated to take approximately 30 minutes to fill in.

**Table 2 T2:** Assessments in The DOMUS study

	**Investigators**	**Patient**	**Caregiver**	**Bereaved**^ **a** ^
Medical History	• Cancer Diagnosis, Co-morbidity, Time of Cancer Diagnosis, Current Disease Stage, ECOG Performance Status etc.	Baseline		
Reported Outcomes (questionnaires)	• Relationship Status, Children, Education	Baseline	Baseline	
	• Wishes for place of care and treatment	Baseline	Baseline	
		Week 2,4,8	Week 2,4,8	
		6 months	6 months	
	• Quality of life questionnaire – Core (EORTC-QLQ-C30) [34]	Baseline		
		Week 2,4,8		
		6 months		
	• Edmonton Symptom Assessment System (revised version) (ESAS-r) [35]	Baseline		
		Week 2,4,8		
		6 months		
	• Hospital Anxiety and Depression Scale (HADS) [36]	Baseline		
		Week 2,4,8		
		6 months		
	• Symptoms priority	Baseline		
		Week 2,4,8		
		6 months		
	• Symptom Checklist-92, anxiety and depression subscales (SCL-92) [37]	Baseline	Baseline	Week 2
		Week 2,4,8	Week 2,4,8	2, 7, 13, 19 months
		6 months	6 months	
	• Modified Medical Outcomes Study Social Support Survey (mMOS-SS)^b^[38]	Baseline	Baseline	Week 2
				2, 7, 13, 19 months
	• Dyadic Coping Inventory (selected subscales) (DCI)^b^[39]	Baseline	Baseline	
		Week 2,4,8	Week 2,4,8	
		6 months	6 months	
	• Relationship ladder^b^[40]	Baseline	Baseline	
		Week 2,4,8		
		6 months		
	• Zarit Burden Interview (ZBI) [41]		Baseline	
			Week 2,4,8	
			6 months	
	• Experiences in Close Relationships-Short Form (ECR) [42]		Baseline	7, 13, 19 months
	• Medical Outcomes Study Short Form (SF-36) [43]		Baseline	Week 2
			Week 2,4,8	2, 7, 13, 19 months
			6 months	
	• Inventory of Daily Widowed Life (IDWL) [44]			Week 2
				2, 7, 13, 19 months
	• Pittsburgh Sleep Quality Index (PSQI) [45]			Week 2
				2, 7, 13, 19 months
	• Prolonged Grief Disorder (PG – 13) [46]			7, 13, 19 months
	• Lifestyle single items			Week 2
				2, 7, 13, 19 months
Blood samples	• Telomere length		Baseline	2 months
Databases^c^	• Number of hospital admissions	From Baseline to 6 months	From Baseline to 6 months	
	• Number of inpatient bed days			
	• Number of outpatient visits to hospitals			
	• Number of visits to GP			
	• Number of visits to the emergency room			
	• Number of visits to the emergency physician			
	• Number of visits to specialists			
	• Treatments in public hospitals			
	• Prescribed drugs			
	• Place of care and death			
Healthcare services	• Health insurance charges	From Baseline to 6 months	From Baseline to 6 months	
	• Pharmacy prices			

^a)^The bereaved is the primary caregiver, ^b)^Only patients with participating relatives, ^c)^The National Patient Register, Health Insurance Registry, Medicine Databases.

In addition, patient’s informal caregivers are asked for a blood sample.

Databases will be used to collect data about the patients and caregivers use of healthcare (Table 2). All planned assessments, questionnaires, and medical records are shown in Table 2.

### Statistical methods

#### **
*Sample size estimations*
**

Sample size was calculated considering the primary purpose of this trial, which is to prolong patients’ residence at home and to increase the number of patients who die at home by 15 - 20%. The latter purpose serves as a proxy for the first purpose. With a power of at least 80%, and an effect difference of 15% at a significance level of 0.05, 170 patients are required in each study arm (Ficher´s exact test). On the basis of this and an expected dropout rate of 10-15%, we plan to randomize 380 patients for the study.

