### Trial plan

The trial is completed when the 340 patients have been randomized and after the last patient has been followed six months from baseline. Data collection is estimated to go on for 2 years. However, the caregivers will continue to be followed 19 months after the death of the patients.

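### The article gives two randomisation targets, 340 and 380; completing at 340 removes the dropout allowance on which its own sample size calculation relies

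*Protocol article*

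**What the plan says.** The sample size section (Statistical methods) sizes the trial on deaths at home, used as a proxy for time spent at home. The aim is to "increase the number of patients who die at home by 15 - 20" per cent. The calculation opens "With a power of at least 80" per cent, takes "an effect difference of 15% at a significance level of 0.05", names Fisher's exact test, and concludes that "170 patients are required in each study arm". Losses are then added: "On the basis of this and an expected dropout rate of 10-15%, we plan to randomize 380 patients for the study".

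Three other places give 340:

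- Abstract, Methods/Design: "The planned sample size is 340 in- and outpatients".
- Study design: "Three-hundred-and-forty in- and outpatients in the Department of Oncology, Copenhagen University Hospital, will be randomly assigned".
- Trial plan: "The trial is completed when the 340 patients have been randomized and after the last patient has been followed six months from baseline".

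The second and third speak explicitly of randomised patients. The abstract gives only a planned size.

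**The concern.** In the sample size section, 340 is the number needed after losses and 380 the number to enrol. In the study design and trial plan, 340 is the number to enrol. The same figure cannot be both unless no losses are expected, and the article expects 10-15%.

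The trial plan defines when the trial is complete, so the conflict bears on when enrolment closes. A team that followed it would finish with fewer evaluable patients than the calculation calls for. The Discussion reports slow accrual (66 patients after a year), so the lower number may well be the one used. A later reader could not tell whether closing at 340 was the plan or a shortfall of 40.

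**Working it through.** **Inputs.** From the sample size section: 15-point difference, significance level 0.05, power at least 80%, 170 per arm, dropout 10-15%, 380 to randomise. From Randomization: 1:1 allocation. Two assumptions are needed. The test is taken as two-sided, because one-sided formulas peak at 150 per arm and never give 170. The control home-death rate is taken as 26%, the 2005 national figure in the Background, because the calculation states none.

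**Step 1: reproduce 170 per arm.** For 26% vs 41% (mean 0.335, d = 0.15), the uncorrected formula is

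n = [1.960 × √(2 × 0.335 × 0.665) + 0.842 × √(0.26 × 0.74 + 0.41 × 0.59)]² / 0.15² ≈ 154.2, rounded up to 155.

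With the continuity correction, n′ = (n/4) × [1 + √(1 + 4/(n × d))]² ≈ 167.3, rounded up to 168. Exact enumeration of Fisher's test first reaches 80% power at 167 per arm, and 170 per arm gives 80.9%. So 26% roughly reproduces the stated figure. The uncorrected formula also gives exactly 170 at 35% vs 50%.

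**Step 2: reproduce 380.**

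- 340 / (1 − 0.10) = 377.8, so 378; this is about 380.
- 340 / (1 − 0.15) = 400.
- Dropout that 380 can absorb: 1 − 340/380 = 10.5%.

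So 380 matches the lower end of the dropout range and not the upper end.

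**Step 3: patients left under each target.**

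| Randomised | 10% lost | 15% lost |
|---|---|---|
| 340 | 306 (153 per arm) | 289 (144-145 per arm) |
| 380 | 342 (171 per arm) | 323 (161 per arm) |

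**Step 4: exact two-sided Fisher power, 26% vs 41%.**

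| Per arm | Power |
|---|---|
| 170 | 80.9% |
| 161 | 78.7% |
| 153 | 76.1% |
| 145 | 74.0% |

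Randomising 340 therefore costs 80.9 − 76.1 = 4.8 points at 10% loss and 80.9 − 74.0 = 6.9 points at 15%. Randomising 380 with 15% loss costs 80.9 − 78.7 = 2.2 points.

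**Step 5: sensitivity to the unstated control rate (15-point difference, exact Fisher).**

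| Control rate | 170 per arm | 153 per arm | 145 per arm |
|---|---|---|---|
| 15% | 89.7% | 86.3% | 84.1% |
| 20% | 85.2% | 80.9% | 78.5% |
| 26% | 80.9% | 76.1% | 74.0% |
| 30% | 78.8% | 74.4% | 71.2% |
| 40% | 75.5% | 70.2% | 69.4% |
| 51% | 78.1% | 73.3% | 69.8% |

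At 20% or lower, power holds up better, but about 150 or fewer per arm would then be required, which does not fit 170. At 30%, 40% and 51%, 170 per arm already falls short of 80% by Fisher's test before any loss. The other route to 170, the uncorrected formula at 35% vs 50%, gives 80.2% at 170 per arm, 75.9% at 153 and 73.6% at 145. Both routes that reproduce 170 thus put the result at about 74-76%.

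**The case against.** Four points can be made on the other side.

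**Place of death is not a questionnaire item.** Table 2 lists it under databases, so a patient who stops returning questionnaires need not be lost for this outcome, and real losses could be below 10-15%. This stands in part. It makes the size of the loss uncertain, but the article itself applies the 10-15% to this calculation. A reader might infer that all 340 will have a known place of death. The document does not support that. The database items appear to run from baseline to six months, no death register is named among the sources, and a patient alive at six months has no place of death in that window. The Discussion also says that the ECOG 2-4 criterion was dropped, partly to study earlier care, which may add survivors.

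**The control rate is unstated, so the shortfall is conditional.** This stands. A reader might infer that power must fall below 80% whatever the rate; at 15% it does not. A reader might also take the Background's 51% home deaths under standard care, from a cited trial in mixed diagnoses, and conclude that power drops to 70-73%. That is not a fair measure of this error: at 51% even 170 per arm gives only 78.1%, so part of the gap has nothing to do with dropout.

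**The aim extends to 20 points.** At that difference, 144 per arm gives 91-93% for control rates from 26% to 51%. This is correct, but the stated calculation is set at 15 points.

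**The gap between 380 and 400 is minor.** Agreed: it is secondary to the conflict between 340 and 380.

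**Conclusion.** The contradiction is explicit and has to be corrected. The calculation requires 340 after losses and plans to randomise 380, while the study design and trial plan randomise 340 and complete at 340. With the article's own dropout, 289-306 patients remain, 34 to 51 short of its stated requirement.

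The consequence for power is moderate and conditional: from about 81% to about 74-76%. It rests on a two-sided Fisher test, a 15-point difference, an assumed 26% control rate, and 10-15% loss that truly removes patients from the place-of-death comparison. The case for correction rests on the conflicting numbers, not on any particular power figure. As a secondary matter, 380 covers about 10.5% dropout rather than the full stated range; at 15% loss it leaves 323 patients and about 79% power at the same control rate.

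**What to change.** Use one randomisation number in the abstract, study design, sample size section and trial plan. In the sample size section, state the assumed control home-death rate and what counts as dropout for place of death.

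- **If 340 randomised is kept:** delete the 380 and restate the power for the number expected to be evaluable, about 74-76% at a 26% control rate with 10-15% loss. Do not claim place of death for all 340 unless follow-up for it extends to death.
- **If 380 is kept:** change the abstract, study design and trial plan to 380, and state that this covers about 10.5% dropout. Covering 15% would take 400.

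The first option costs wording and a less favourable power figure. The second costs wording and the recruitment of 40 more patients than the trial plan now requires, which matters given the accrual reported in the Discussion.
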